#### 2.12.2. Data Preprocessing

##### Missing Data Management Imputation

Routine missing data diagnostics will first be conducted: the proportion of missing values for each variable will be reported and visually illustrated by means of a missing data heatmap. The correlation of missingness between variables will be reported pairwise and a dendrogram will be used to provide a comprehensive visual representation of pairwise comparisons.

Multiple Imputation by Chained Equations using Random Forests (MICE RF) will be implemented to impute missing values, based on the algorithm proposed by Doove et al. [93]. Multiple imputation is today’s state-of-the-art solution for handling missing data and, by incorporating a recursive partitioning technique in the MICE framework, this method can fit interactions, non-linear relationships, and complex distributions within the data. As a result, more precise and reliable imputations are achievable as the gains in preserving interaction effects have been found to outweigh the somewhat higher biases for main effects [93], a tradeoff we consider justified given our presumption of interaction effects. Importantly, the missing data mechanisms assumed by MICE (missing completely at random [MCAR] or missing at random [MAR]) are almost impossible to definitively establish [94] and the missing data diagnostics mentioned above are suited only to intuit the plausibility of MCAR. To alleviate this issue, we will include available auxiliary variables in the imputation model that are predictive of missingness but will not be used in the data analysis stages, namely hyperlipidaemia, smoking status, and 30-day NIHSS. Incorporating auxiliary variables has been shown to make the MAR assumption more plausible [95,96], all the while posing little risk to the precision or bias of estimates.

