To avoid information leakage, imputation will be performed strictly within each training fold of the inner and outer cross-validation loops, and never on the full dataset before splitting. Any necessary scaling or encoding of continuous variables (e.g., NIHSS, mRS, OTT, VKA days) will likewise occur within-fold. A total of 10 imputation cycles will be performed before aggregating the respective models’ outputs (i.e., computing the mean for continuous variables and selecting the mode for binary variables), with 100 trees per RF model. The constituent features of CHA_2_DS_2_-VASc will be imputed and the score calculated after imputation is complete, which has been reported to be the more appropriate approach for sumscores constructed from relatively few variables [94]. Of note, MICE RF will be performed separately for AF and non-AF cohorts because the validity of later analyses depends on the non-AF cohort having in no capacity shaped the models trained on the AF cohort.

Although missing data ubiquitously occur in RCTs, VISTA did not record how contributing trials handled missing data.

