##### Imputation Diagnostics

Convergence of the MICE RF algorithm will be examined using trace plots of the mean and variance of the imputed values across iterations, ensuring that these metrics stabilise over the 10 imputation cycles. The distributions of observed and imputed values will be compared using density plots and histograms, visualising whether the imputed data are faithful to the observed data’s distributional characteristics. Finally, despite the fact that the missing data assumptions of complete case analysis (CCA) are stronger than those of MICE [97], we will perform a sensitivity analysis by comparing the results of our primary analyses on both the imputed and complete-case datasets.

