Instantiating the models using the hyperparameters determined by the above procedure, we will retrain them in order to leverage all patients in ***T*.** The resulting models will be considered final and subjected to evaluation on ***t*** in the next section (see “Model Evaluation”). At this stage, training performance will be recorded. Specifically, we will report the area under the receiver operating characteristic curve (AUC), F1 score, accuracy, precision, sensitivity, and specificity. Coefficients and ORs (exponentiated coefficients) with 95% confidence intervals (CIs) will be reported for LR, and the hierarchy of predictor variables in descending order of gain (its internal feature importance metric) will be provided for XGBoost. Individual decision trees within the XGBoost model will supplementarily be made available.

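### Ten imputation cycles are reduced to one mean or mode per missing cell before scoring and modelling, so the plan's multiple imputation is in effect single imputation

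*Protocol article*

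**What the plan says.** The protocol article, Section 2.12.2 (Missing Data Management Imputation), adopts the method in these words: "Multiple Imputation by Chained Equations using Random Forests (MICE RF) will be implemented to impute missing values". The reason given is that "Multiple imputation is today’s state-of-the-art solution for handling missing data". The authors also argue that random forests preserve interactions and complex distributions, and they accept somewhat more bias in main effects in return.

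The same section then fixes how the results are combined: "A total of 10 imputation cycles will be performed before aggregating the respective models’ outputs", by "computing the mean for continuous variables and selecting the mode for binary variables". The constituent features of CHA2DS2-VASc "will be imputed and the score calculated after imputation is complete". Section 2.4 states that all of these features except age are binary.

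Imputation Diagnostics asks for trace plots, "ensuring that these metrics stabilise over the 10 imputation cycles", and plans a sensitivity analysis "comparing the results of our primary analyses on both the imputed and complete-case datasets".

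Intervals are planned in three places:
- Section 2.12.4: bootstrap intervals for the validation AUC.
- Model Building: "Coefficients and ORs (exponentiated coefficients) with 95% confidence intervals (CIs) will be reported for LR".
- Model Evaluation: bootstrap and DeLong intervals for the test-set AUC.

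No section describes several retained datasets, a pooling rule, or re-imputation inside the bootstrap.

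**The concern.** Multiple imputation works because the completed datasets differ. Their spread carries the uncertainty about the missing values, and the random draws keep the distribution of each variable intact. Taking a mean or mode over the cycles removes both properties before any analysis begins.

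Two consequences follow. First, a binary feature is no longer drawn in proportion to its probability but is set to its more likely value. That alters prevalences, joint patterns and the score, and it works against the stated reason for choosing random forests. Second, standard errors and bootstrap samples treat the filled-in values as observed. The step precedes the primary validation of CHA2DS2-VASc and all updating models, so whatever distortion it causes passes into both.

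**Working it through.** **What the text fixes.** The article states no figure on this point that could be reproduced. Two readings of the ten cycles are possible. If they are ten imputations, the mean or mode merges them into one. If they are chain iterations, as the trace-plot sentence treats them, there is one chain whose states are merged. Either way each missing cell receives one value.

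**The mode rule.** Let p be a patient's conditional probability that the feature is present, and treat the ten cycles as independent draws. The mode is present when at least six draws are:

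P(present) = Σ (k = 6 to 10) C(10,k) p^k (1−p)^(10−k); P(tie) = C(10,5) p^5 (1−p)^5.

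| p | P(present) | P(tie) |
|---|---|---|
| 0.2 | 0.006 | 0.026 |
| 0.3 | 0.047 | 0.103 |
| 0.4 | 0.166 | 0.201 |
| 0.5 | 0.377 | 0.246 |
| 0.6 | 0.633 | 0.201 |
| 0.7 | 0.850 | 0.103 |
| 0.8 | 0.967 | 0.026 |

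The article gives no rule for ties.

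**Effect on prevalence.** With missing fraction f, true prevalence π and the same probability for all patients, completed prevalence = (1−f)π + f·P(present), ties set to absent:
- π = 0.20: 0.9×0.20 + 0.1×0.006 = 0.181 at 10% missing; 0.142 at 30%.
- π = 0.30: 0.275 at 10%; 0.224 at 30%.
- π = 0.70: 0.715 at 10%; 0.745 at 30%.

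Equal probabilities are the extreme case, since they mean an uninformative imputation model. If probabilities vary between patients (logit-normal, SD 1), the share of missing cells set to present is 5.9% at π = 0.20, 15.1% at 0.30 and 75.6% at 0.70. The distortion shrinks but remains.

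**Effect on intervals.** The inputs were n = 2763 (Section 2.3) and, by assumption, a true log odds ratio of 0.693, one binary feature with nominal prevalence 0.2 or 0.7, values missing completely at random, ten draws, and 300 replicates. The imputation model was logistic, not random forest, and included the outcome and one covariate. Rubin's total variance is T = W + (1 + 1/10)B, with W the within- and B the between-imputation variance. Collapsing leaves W alone, taken from the single filled-in dataset.

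| Prevalence | Missing | Method | Mean log OR | Empirical SD | Mean SE | Coverage |
|---|---|---|---|---|---|---|
| 0.2 | 10% | pooled | 0.694 | 0.153 | 0.147 | 93.7% |
| 0.2 | 10% | collapsed | 0.727 | 0.164 | 0.141 | 90.0% |
| 0.2 | 30% | pooled | 0.708 | 0.163 | 0.168 | 96.0% |
| 0.2 | 30% | collapsed | 0.831 | 0.211 | 0.146 | 72.7% |
| 0.7 | 10% | pooled | 0.700 | 0.159 | 0.155 | 94.7% |
| 0.7 | 10% | collapsed | 0.752 | 0.168 | 0.151 | 91.3% |
| 0.7 | 30% | pooled | 0.690 | 0.172 | 0.177 | 95.0% |
| 0.7 | 30% | collapsed | 0.863 | 0.215 | 0.162 | 75.7% |

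The coverage loss is 3.7 and 3.4 points at 10% missing, and 23.3 and 19.3 points at 30%. With 300 replicates, the simulation error of one coverage figure near 90% is √(0.90×0.10/300) = 1.7 points. The loss at 10% is therefore modest and imprecise, while the loss at 30% is clear.

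**The case against.** Several points on the other side have weight.

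- **Direction.** A reader might infer that most missing comorbidities become absent and that the score is biased down. The article gives no prevalences, and the rule raises prevalence where a feature is present in most patients. Opposite errors can partly cancel in the sum score. This stands: only movement towards the majority class can be claimed.
- **Size.** Section 2.3 describes the cohort as having these variables documented, and missingness may be small. A feature with 30% prevalence falling to about 5% among imputed cells requires independent draws and an uninformative imputation model; with varying probabilities the figure is 15.1%. If the cycles are successive states of one chain, the binomial figures are only approximate. This stands too.
- **Primary measures.** A separate simulation of the score (four comorbidities at assumed prevalences of 0.25 to 0.70, event rate about 8%) moved the AUC by only 0.003 to 0.004 at 10% missing and 0.006 to 0.007 at 20%. It did not cover calibration, net benefit or interval coverage, so it limits the concern about discrimination and no more.
- **Safeguards.** The complete-case intervals contain no imputed values, and the planned histograms could expose the distortion. Neither restores the missing variance, and the article itself says complete-case analysis needs stronger assumptions.
- **Prediction needs no pooling.** Deterministic imputation can serve a pure prediction task. But this plan also reports odds ratios with intervals, calibration and net benefit, and rests its choice on multiple imputation.
- **Wording.** The aggregated outputs might be taken to be those of the prediction models. The sentence averages variables and goes on to give the number of trees per forest, so the imputation forests are meant.

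**Conclusion.** The point holds in this form: the plan describes single imputation under the name of multiple imputation, the mode rule moves binary features to the majority class, and every interval computed on the imputed data omits between-imputation variance. This follows from what the article states, not from something left to a fuller document.

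The size cannot be fixed from the article. On the assumptions above, coverage of the log odds ratio falls by about 3 to 4 points at 10% missing and 19 to 23 points at 30%. The documents do not support saying that the score is biased down, that every interval in the study is affected, or that the primary AUC is materially wrong. The change should be made, and it is easiest before the analyses are run. Because the missing fraction is unknown, the point does not by itself invalidate the plan.

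**What to change.** Delete the mean and mode aggregation from Section 2.12.2 and replace it with the following:

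1. State the number of imputations (m of at least 10) separately from the number of chain iterations, and apply the trace plots to the iterations.
2. Keep the m completed datasets, with imputation still confined to training folds where the plan requires it. Compute CHA2DS2-VASc and evaluate it within each dataset.
3. Pool logistic coefficients, AUC on the logit scale, calibration-in-the-large and calibration slope by Rubin's rules, or nest the imputation inside the bootstrap.
4. Tune hyperparameters once and refit per imputation. Average predicted risks and net benefit over imputations.
5. Average SHAP main and interaction values over imputations before the tier assignment in CPR Development, so that one point score per model results.

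The cost is about tenfold refitting, slightly wider intervals, and a short added rule for arriving at the single published prediction rule, including how the per-imputation XGBoost trees are reported.

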##### Imputation Diagnostics

Convergence of the MICE RF algorithm will be examined using trace plots of the mean and variance of the imputed values across iterations, ensuring that these metrics stabilise over the 10 imputation cycles. The distributions of observed and imputed values will be compared using density plots and histograms, visualising whether the imputed data are faithful to the observed data’s distributional characteristics. Finally, despite the fact that the missing data assumptions of complete case analysis (CCA) are stronger than those of MICE [97], we will perform a sensitivity analysis by comparing the results of our primary analyses on both the imputed and complete-case datasets.

##### Variable Encoding

Comorbid features, tobacco use, IVT, recurrence, and mortality will be encoded as: absent = 0 and present = 1. Sex will be encoded as: male = 0 and female = 1, as stipulated by CHA_2_DS_2_-VASc. The number of days of VKA use over 90-day follow-up will be treated as a continuous variable.

Age requires a more nuanced approach to preserve the structure of the existing CPR. For the validation analyses, age will be encoded as usual: age < 65 years = 0, 65–74 years = 1, and ≥75 = 2. For the updating analyses, the age categories (<65, 65–74, ≥75 years) will be one-hot encoded. This approach involves creating three binary variables and thereby avoids the introduction of an artificial ordinal scale that could imply a linear progression of risk across age groups. As such, it respects the non-linear risk increments that have been reported with advancing age and acknowledged by the existing CPR. Age categories will be fixed, and, in logistic regression, one dummy variable will be dropped from each categorical set to avoid the dummy variable trap.

All other variables (mRS, NIHSS, OTT) will be kept in their original format.

#### 2.12.3. Descriptive Statistics

The Shapiro–Wilk test will be performed to test for normality. Continuous and ordinal variables with normal distributions will be reported as means and standard deviations, while non-normally distributed variables will be reported as medians and interquartile ranges. Binary variables will be reported as counts and ratios of valid observations. All descriptive statistics will be provided both with and without imputation of missing values. Comparisons between groups will be made using the independent samples t-test, the Kruskal–Wallis test, and χ^2^ test, as appropriate.

Primary: How well does CHA_2_DS_2_-VASc capture 90-day AFAIS recurrence risk in terms of discrimination, calibration, and clinical utility? (Clinical utility performed against updated CPRs, see Tables 3 and 4.) Secondary: How well does CHA_2_DS_2_-VASc capture: 7-day recurrence, 7- and 90-day HT, 90-day decline in functional status, and 90-day all-cause mortality? Exploratory: How well does CHA_2_DS_2_-VASc capture 90-day recurrence and secondary outcomes for non-AF AIS patients?	Primary: Discrimination of CHA_2_DS_2_-VASc for 90-day AFAIS recurrence risk is unsatisfactory (AUC < 0.6), at worst, and modest (<0.7), at best. Calibration for 90-day recurrence also leaves much room for improvement. Secondary: As above.	Discrimination assessed using AUC and calibration curves. Calibration assessed using calibration curves, slopes, and Brier scores. Additional metrics: F1 score, accuracy, precision, sensitivity, specificity, Youden index, PPV, NPR, PLR, NLR.	Primary: A minimum of 680 patients deemed necessary, see Appendix S5.3 in Supplementary Materials file S3. Entire AF dataset will be used, comprising 2763 AFAIS patients. Secondary: As above. Exploratory: Entire non-AF dataset will be used, comprising 7809 AIS patients.	Compute AUCs with 95% CIs using 1000 bootstrap replicates. Produce calibration curves (and report calibration slopes) to illustrate calibration. Calibration curves also serve as alternative to ROC curves, as they illustrate true and false positive rates across different risk thresholds and thus help visualise discrimination. Compute Brier scores. Compute additional metrics.	Discrimination for each outcome will be classified as follows [101]: AUC of 0.81–0.90 = good, 0.71–0.80= fair, 0.61–0.70 = modest, and 0.51–0.60 = poor. In practice, calibration is more vulnerable to geographic and temporal heterogeneity than discrimination [102,103,104,105]. We thus stress that calibration is at least as important as discrimination [77,102]. Clinical utility via DCA will go beyond discrimination and calibration, considering them both at the same time [106], as well as individual preferences.

#### 2.12.5. Updating

##### Models

LR, XGBoost, and MLP classifier models will be used to establish the updated CPR. LR and XGBoost will power our primary analyses, and MLP our secondary analyses.

##### Primary Analysis

LR will serve as our baseline model, which is in keeping with how CPRs have traditionally been developed and reflects the fact that regression analysis tends to perform remarkably well [107]. As a matter of fact, the predictive performance of ML models in the context of CPMs has been reported to be non-superior to that of LR when comparisons had low risk of bias [60]. As an interpretable model, LR will enable us to unequivocally ascertain whether a feature has a positive or negative impact on the probability of an outcome by virtue of the odds ratio (OR).

XGBoost will be used to free our primary analysis from the linear separability constraint of LR. As a decision tree ensemble method, XGBoost iteratively fits the data to minimise residuals by adding trees that focus on areas where previous trees underperformed. By combining the predictions of multiple trees, XGBoost can capture complex, non-linear interactions, making it particularly effective for irregular decision boundaries where linear models fall short.

##### Secondary Analysis

DL will be used to leverage the non-AF cohort data. A transfer learning strategy will be adopted: the MLP (a multilayered feed-forward neural network) will be pretrained on the non-AF dataset, and the best-performing pretrained model will be transferred to the AF dataset for fine-tuning. In other words, the model will initially learn from the larger dataset and then refine its parameters downstream on the target dataset, enhancing its predictive performance for the latter. This technique exploits the layer-wise modular architecture of neural networks, that is, the fact a network can be constructed by removing all layers after a particular layer and appending a new connected layer with a different configuration of neurons and initial weights. As a result, the MLP will have learnt from 10,572 AIS patients, all the while prioritising the 2763 with AF. Indeed, the pretraining paradigm has become dominant because it has enabled the use of neural networks in small datasets, where it would not be cautious to train models from scratch [108]. Generally, the more similarity between the datasets, the more benefits conferred by transfer learning, including higher asymptotic accuracy, enhanced generalisability, and accelerated convergence. We consider our situation well-suited to this technique: the features of CHA_2_DS_2_-VASc are known to increase risk of AIS in patients without AF [40,71] and CHA_2_DS_2_-VASc does not incorporate AF-related parameters that impact AIS risk, such as duration of AF and left atrium/left atrial appendage (LAA) size, function, and morphology [101]. It has even been reported that CHA_2_DS_2_-VASc may be equally discriminative in the absence of AF [40].

Of course, no preprocessing parameters or summary statistics will be carried over from the non-AF to AF datasets. Pretraining (including its internal validation) will use only non-AF data, and during AF model development, all preprocessing will be fit within AF training folds only, with the AF hold-out test set untouched until final evaluation.

#### 2.12.6. Regularisation

##### Multicollinearity

Multicollinearity is a common phenomenon in clinical prediction modelling and means that the data offers limited information on how the explained variance in the outcome should be distributed over the collinear predictors [109]. Although this is generally not considered problematic with regard to predictive performance [110], we will report the variation inflation factor (VIF) to acknowledge that there may not be just one way, but multiple ways, to construct the CPR that are equally valid in our data [111]. VIF > 5 will be considered indicative of significant multicollinearity.

##### Regularisation Techniques

LR will be instantiated with L2 regularisation (ridge regression). L2 introduces a penalty proportional to the sum of the squared coefficients to the loss function. This shrinks the coefficients of less important features and discourages an overly complex model, thereby stabilising the estimates and improving generalisability.

For XGBoost, we will use built-in tree-specific regularisation hyperparameters to constrain model complexity and mitigate overfitting. See “Hyperparameter Tuning” below.

MLP will be instantiated with L2 (weight decay) and dropout, complementary regularisation techniques that limit the magnitude of weights and prevent complex coadaptation of neurons, respectively. As a result, the network will be prevented from becoming too complex or overly dependent on specific neurons and encouraged to learn more generalised patterns.

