The sample sizes derived from steps 1, 2, 3, and 4 were 288, 344, 680, and 459 patients, respectively. We therefore deemed a minimum total sample size of 680 patients necessary for CPR development. Given that our sample size is 2763 patients and the fact that we will perform validation and updating (and not development from scratch), we contend that our regression analyses are adequately powered. Of note, 75% of our dataset (*n* = 2072 patients) will be used for regression model training and the remaining 25% (*n* = 691 patients) will be reserved for testing. The fact our test set alone exceeds the required 680 patients further supports our sample size.

ML and DL techniques are inherently more data-intensive than regression [85]. This is because the number of predictors they consider far exceeds that of regression, even when the same set of predictors is considered, because they examine multiple interaction terms [84]. Unfortunately, guidance for a priori sample size calculations is currently lacking for most ML/DL techniques [86]. However, if closely related data are readily available, it has been suggested that inspecting model learning curves in the related dataset can be valuable to estimate the required sample size for the main dataset [87,88]. We will therefore explore the observed power of our non-regression models by means of learning curves on our non-AF dataset, as well as via a key information theoretic metric: Kullback–Leibler (KL) divergence.

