### 2.8. Handling Class Imbalance

To address anticipated class imbalance (recurrence rates within the 0.05–0.25 range), class-weight adjustments will be applied in LR, XGBoost, and MLP models. Decision thresholds will be optimised within validation folds using Youden’s J and F1 score. Predicted probabilities will be calibrated using Platt scaling or isotonic regression, with the choice depending on sample size and distributional characteristics (Platt for smaller samples, isotonic when sufficient data allows). Thresholds used in decision curve analysis will be derived from these probabilities calibrated on validation data to ensure clinically meaningful comparisons.

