##### Hyperparameter Tuning

Each model class is characterised by a unique suite of hyperparameters that play a pivotal role in shaping performance. Manual trial-and-error to configure these values is computationally irreproducible and prone to bias [112]. To avoid obfuscating our models’ internal architectures, we will automate hyperparameter optimisation using grid search within the predefined hyperparameter search spaces tabulated below. The search spaces are intentionally small, as limiting the number of adjustable elements is another means to impose constraints on complexity (Table 2).

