##### Model Building LR and XGBoost

We will instantiate LR with L2 regularisation and default hyperparameters (i.e., C = 1, max_iter = 100, solver = ‘lbfgs’), and XGBoost with default hyperparameters (i.e., n_estimators = 100, learning_rate = 0.1, max_depth = 3, objective = ‘binary:logistic’).

The AF dataset will be randomly split into two parts: training (***T***, 75%) and test sets (***t***, 25%), ensuring that the distribution of outcomes is preserved across both sets. LR and XGBoost models will each be trained, hyperparameter-tuned, and retrained on the training set (***T***), while the independent test set (***t***) will be withheld for final evaluation (Figure 1).

To achieve robust final models, we will employ nested cross-validation (CV) for training and hyperparameter tuning. Nested CV is particularly effective for small to moderately sized datasets because it promotes generalisability by ensuring that the hyperparameter tuning process does not contaminate the internal evaluation phase [113]. To this end, a 5 × 2 setup will be utilised, consisting of 5-fold CV in the outer loop and 2-fold CV in the inner loop (Figure 2). The set ***T*** will first be split into five equal parts. In each fold of the outer loop, one part (20% of ***T***) will serve as the intra-model test set ***T_t_*** while the remaining 80% will serve as the intra-model training set ***T_T_***. Each outer loop iteration will be subjected to an inner loop that further splits ***T_T_*** into two equal parts, using one as the true training set ***T_T_train_*** and the other as the validation set ***T_T_val_***, and alternating them over the two folds. The primary selection metric in the inner CV will be log loss (binary cross-entropy), with ties broken by calibration performance (Brier score).

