##### CPR Development

SHAP will be used to ‘translate’ model insights into CPRs. Mean—and not mean *absolute*—SHAP values will be used in order to preserve information on the directionality of feature importance. The decile rank of each of the eight mean SHAP values from each model will be calculated and a dot plot will be provided to visualise each feature’s mean SHAP value relative to others. (We speak of eight mean SHAP values because we have eight predictor variables corresponding to the features of CHA_2_DS_2_-VASc, namely five comorbid items, sex, and *two* age categories [65–74 years and ≥75 years]). The 25th, 50th, and 75th percentiles of the eight mean SHAP values will be computed. We will subsequently rank the features from most to least important and sort them into three tiers: (1) the lower tier grouping features with mean SHAP values below the 25th percentile, (2) the middle tier grouping features with mean SHAP values between the 25th and 75th percentiles, and (3) the upper tier grouping features with mean SHAP values above the 75th percentile. Features belonging to the lower, middle, and upper tiers will be assigned one, two, and three points, respectively. The purpose of a larger middle tier is to avoid over- or understating the importance of features by promoting stability over frequent changes with minor shifts in model parameters. In the rather unlikely event that one or more features will have negative mean SHAP values and local SHAP value distributions that are consistently left of zero on the beeswarm plots, zero points will be assigned, because their inclusion would degrade 90-day recurrence predictive performance. Ties at quantile cut-points will be resolved conservatively by assigning them to the higher category (e.g., features tied at the 75th percentile will enter the upper tier). The resulting CPRs will be summarised in tabular form and given an acronym in likeness to CHA_2_DS_2_-VASc.

If the dot plot suggests that the distribution of mean SHAP values is very skewed or concentrated, the above-defined tiers will probably inadequately capture features of lower, intermediate, and higher importance. In this eventuality, we will tailor tier boundaries using quantile-based binning. After adapting the tier setup to the observed clusters, we will define lower, middle, and upper tiers whose features will be assigned one, two, and three points, respectively.

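### The XGBoost depth grid starts at 3, so an additive or pairwise booster can never be selected; adding depths 1 and 2 is a cheap improvement if the inner log loss is scored on calibrated or unweighted probabilities

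*Protocol article*

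**What the plan says.** Under Regularisation Techniques the protocol article says of XGBoost that "we will use built-in tree-specific regularisation hyperparameters to constrain model complexity and mitigate overfitting", and it refers to Hyperparameter Tuning. That section gives the rationale: "The search spaces are intentionally small, as limiting the number of adjustable elements is another means to impose constraints on complexity".

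Model Building LR and XGBoost sets the starting values at "n_estimators = 100, learning_rate = 0.1, max_depth = 3". Table 2 tunes three settings: n_estimators (50, 100, 200), learning_rate (0.01, 0.1, 0.2) and max_depth (3, 5, 7, 9).

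For choosing among them, "The primary selection metric in the inner CV will be log loss (binary cross-entropy"), with the Brier score breaking ties. Section 2.8 anticipates "recurrence rates within the 0.05–0.25 range" and says "class-weight adjustments will be applied in LR, XGBoost, and MLP models". The same section plans Platt or isotonic calibration, but does not say whether calibration comes before the inner-fold log loss is computed.

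CPR Development states that "we have eight predictor variables corresponding to the features of CHA_2_DS_2_-VASc". It builds each CPR from mean SHAP main effects and an augmented CPR from pairwise SHAP interaction values. Pairs above the 90th percentile of 28 are taken, with at most three pairs and three points.

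**The concern.** The stated aim of the grid is to limit complexity, yet its lowest depth equals the starting depth. Tuning can keep the trees as they are or deepen them, and can never simplify them. Depth 3 already admits three-way interactions. The two forms that match the deliverable are outside the search: depth 1 (main effects only) and depth 2 (main effects and pairs).

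Two things are at stake. XGBoost is a primary-analysis model set beside LR, and a tuning floor would be confounded with the difference between the methods. Table 3 also asks whether synergistic or other non-linear interactions improve prediction, and a booster that cannot return an additive fit cannot answer no.

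**Working it through.** **Figures in the plan.** The split reproduces: 2763 × 0.75 = 2072.25 and 2763 × 0.25 = 690.75, given as 2072 and 691. Eight features give 8 × 7 / 2 = 28 pairs, as stated. The protocol gives no figure for the effect of tree depth.

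**What the grid permits.** Six binary items and three age groups give 2^6 × 3 = 192 patterns. A tree path can use at most 6 + 2 = 8 informative splits, so depth 9 never binds. An inner training half holds 2072 × 0.8 / 2 ≈ 829 patients, or about 41 to 83 events at 5 to 10% recurrence. The grid has 3 × 3 × 4 = 36 points, and 3 × 3 × 6 = 54 with depths 1 and 2 added.

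**Simulation.** There were 50 replicates per scenario, with 2072 training patients, eight features, 5 × 2 cross-validation, log-loss selection and the Table 2 grid. The boosting routine agreed with the xgboost library to about 1e-6 on the margins. Performance was computed exactly on the known population. These inputs are assumptions, because the documents do not give them:
- feature prevalences and coefficients;
- true AUC of 0.58 to 0.75;
- library defaults for untuned settings (lambda 1, min_child_weight 1, gamma 0);
- averaging the inner log loss over the outer folds to choose the final settings.

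Results with additive truth and no class weights (planned grid → grid with depths 1 and 2 added):

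| Event rate, true AUC | XGBoost AUC | LR AUC | Non-additive share of logit variance | Depth 1 chosen when offered |
|---|---|---|---|---|
| 0.05, 0.65 | 0.607 → 0.622 | 0.632 | 29% → 5% | 80% |
| 0.10, 0.58 | 0.549 → 0.552 | 0.565 | 37% → 12% | 66% |
| 0.10, 0.65 | 0.622 → 0.637 | 0.641 | within 10–37% → 2% | 90% |
| 0.10, 0.75 | 0.729 → 0.744 | 0.745 | 10.5% → 0.2% | 98% |
| 0.25, 0.65 | 0.635 → 0.645 | 0.646 | 13% → 0.2% | 98% |

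Under the planned grid, depth 3 was chosen in 90 to 100% of these runs, which is how a search cut off at its lower edge behaves. The AUC gain is 0.003 to 0.015. The planned booster trails LR by 0.011 to 0.025. The floor accounts for between 0.0029 of 0.0155 (19%) and 0.0146 of 0.0158 (92%) of that gap. Three pairs entered the augmented CPR in every planned-grid run, against 0.06 to 0.94 on average with the wider grid.

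**With class weights.** At a 25% event rate and true AUC 0.75, the wider grid still helped: AUC 0.739 → 0.747, non-additive share 6.5% → 0.3%. At a 10% rate, true AUC 0.65 and raw log loss, it changed nothing. Both grids chose depth 5 to 9, with AUC 0.579 and a non-additive share of 66%. Restricting the search to depths 1 and 2 gave AUC 0.628. The deep model nevertheless had the lower raw log loss (0.637 against 0.651), so raw log loss on weighted output ranked the worse discriminator first.

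**Does calibrated scoring cure this?** In a smaller simulation (6 runs per main scenario, xgboost library, additive truth), Platt-calibrated weighted output gave AUC 0.575 → 0.593 and non-additive share 27% → 0%. Unweighted scoring gave 0.578 → 0.593 and 33% → 0%. With weights and raw log loss at 5 to 10% events, both grids chose the same depth 7 to 9 model in every run.

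**If interactions are real.** With two true interactions (10% rate, true AUC 0.70, unweighted), the wider grid was no worse: AUC 0.6805 → 0.6845.

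**The case against.** The protocol gives the main-effects role to LR and brings in XGBoost to capture interactions, which it openly presumes. A depth-1 booster on binary inputs is an additive logit and largely repeats LR. This stands in part: an additive model cannot be selected within XGBoost, but the plan as a whole has one. It does not justify denying XGBoost the chance to find few or no interactions.

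The accuracy effect is small. With 691 test patients and about 69 events at 10%, the Hanley–McNeil standard error of a single AUC of 0.62 is about √(60.7 / (69 × 622)) ≈ 0.038. LR also stayed ahead of the widened grid in every scenario in the table. This stands.

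A reader might infer that spurious interactions make the CPRs predict worse. The calculations do not support that. Under additive truth without class weights, the augmented XGBoost CPR had a higher AUC than its non-augmented form, by 0.002 to 0.008. CPRs from the wider grid were not more accurate. Where the two grids led to different models, their AUC was lower by 0.002 to 0.018 (non-augmented) and 0.003 to 0.025 (augmented); the reason was not traced. The three pairs also come from the percentile rule, which selects about three whenever the values differ and has no test against zero. Adding depth 2 alone would still pass three.

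A reader might also infer that Regularisation Techniques and Table 2 contradict each other because no leaf penalty is tuned. They do not. The text names no specific penalty, and depth, tree number and learning rate do constrain complexity.

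**Conclusion.** The point holds in a limited form. The depth floor is a fact of Table 2 and sits badly with the stated aim of limiting complexity. If the truth is close to additive, the XGBoost model loses about 0.003 to 0.02 in AUC, and roughly 10 to 40% of its fitted logit variance is spurious interaction (6.5% in the weighted 25% scenario). The consequence is a less fair LR–XGBoost comparison and interaction rules that cannot be read as evidence of synergy. Harm to CPR discrimination is not shown.

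The sizes rest on assumed prevalences, coefficients and library defaults. The benefit of the wider grid at low event rates depends on how the inner log loss is scored. This is a cheap improvement, not a defect that invalidates the analysis.

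**What to change.** In the max_depth row of Table 2, list 1, 2, 3, 5, 7 and 9. Depth 1 must be included, because depth 2 alone does not let the interaction step come out empty.

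In Model Building LR and XGBoost, state that the inner log loss is computed on calibrated probabilities (the calibration already planned in section 2.8, applied before scoring) or on unweighted fits. Without this, the added depths do nothing at 5 to 10% event rates.

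Tuning a leaf penalty such as min_child_weight or reg_lambda is optional. Three values would take the grid from 54 to 54 × 3 = 162 points.

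The cost is slightly longer tuning (36 to 54 points) and one added sentence. Deeper trees remain available, so real interactions can still be found. The change should not be presented as improving CPR accuracy, because the simulations do not show that.
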